### Baseline assessment measures

2.3

*All studies*

In all three studies, diagnostic inclusion and exclusion criteria will be confirmed on the Structured Clinical Interview for DSM-5, Research Version [SCID-5-RV,
89], as will the presence of common anxiety and substance use comorbid diagnoses. The Structured Clinical Interview for Sleep Disorders-Revised [SCISD-R,
90] will be used to assess the presence of common sleep disorders at baseline.

*Study 1 and 2*

People interested in participating will be invited to visit the study website (or if internet is not readily available, provided with written documentation where they can review study details), and then complete a consent form and answer an initial screening survey on demographic and inclusion/exclusion criteria (age, sex/gender, currently receiving medical treatment for a diagnosis of BD I or II, presence of lifestyle or physical condition impacting RAR). Those who pass the online screening questions will be invited to an appointment for a screening interview, conducted online in Study 1 (Australia) and in person in Study 2 (India). Interviewers will confirm that the potential participant is engaged in medical care for their BD and confirm consent. To minimise fraudulent engagement with these paid studies,
^
91
^ participants’ identity will be confirmed in Study 1 by presentation of a photo ID during the teleconference. In Study 1 and 2, the exclusion criterion of active suicidality is operationalised as a score of 3, 4, or 5 on the Columbia Suicide Severity Rating Scale [CSSRS,
92].

*Study 3*

In Study 3, participants must be in an episode of mania or bipolar depression at baseline as assessed by a senior psychiatrist of the health service and have a CGI score of 5 and above (markedly ill).

### Primary outcomes

2.4

*Study 1 and 2: Time to relapse*

In Study 1 and 2, the time to relapse of any BD episode (manic, hypomanic, depressive) will be assessed using the LIFE [
5]. The LIFE was developed to retrospectively assess the longitudinal course of psychiatric disorders over extended periods. Weekly data are elicited retrospectively, in an interview format. The method allows for the overall quantification of mood burden, through the interviewer determining ordinal weekly scores for severity of depression and mania. Patients are rated on a 1–6 scale, where 1—no symptoms, 2—residual symptoms, 3—partial remission, 4—does not meet DSM criteria but has major symptoms or impairment, 5—meets definite DSM criteria for an “episode”, and 6—fulfills definite criteria for an “episode” with the presence of either psychotic symptoms or extreme impairment in functioning. By determining whether syndromal symptoms last 2 weeks, relapse into a depressive or manic episode can be determined. The LIFE method has been used in several longer-term studies in BD to determine time to episode occurrence and overall mood morbidity [e.g.,
79–
82]. The retrospective LIFE avoids the problem of participant burden with prospective (e.g., weekly or monthly) measurement in long-term outcome research, and in BD populations has the additional strength of minimising the confound of episode-related impaired insight. Porter and colleagues have recently published an analysis of two studies validating the LIFE’s retrospective weekly estimates against concurrently rated clinician ratings on the MADRS and YMRS.
^
72
^

In Study 1 and 2, LIFE interviews will occur twice in each monitoring epoch (13 weeks, and 26 weeks, with 13 weeks’ retrospection window at each interview). The LIFE is commonly administered at 6-month intervals, and there is reason to believe that the 13-week intervals here will improve the reliability and resolution of our estimate of time to relapse.
^
71
^
^,^
^
77
^ Because of remote recruitment, the LIFE will be conducted by telehealth in Study 1. In Study 2, the LIFE will be conducted in person.

In Study 1 and 2, two types of secondary analysis will be conducted. First, recognising that the number of observed relapses may not be sufficient to support reliable modelling, a secondary analysis will be conducted on the prediction of
*symptom burden* in the follow-up window (three epochs in Study 1, one in Study 2). Weekly symptom burden will be measured on the LIFE on 6-point scales for weekly depression and mania (see above). Second, in all studies, modelling analyses will be re-conducted using the outcome measure of self-reported Quality of Life (QoL), a patient-valued outcome. For the present project, QoL scores have the advantage of being a meaningful variable in both the interepisode cohorts of Study 1 and 2, and the highly symptomatic cohort of Study 3. The BD-specific QoL.BD [short form,
83,
84] will be collected at 13-
and 26-week follow-ups in Study 1 and 2 and at the week 8 endpoint in Study 3.

*Study 3: Treatment response*

The primary outcome variable in Study 3 will be 50% reduction in MADRS or YMRS scores at 8 weeks. The prospective relationship between weekly RAR and weekly symptom assessments (MADRS, YMRS, CGI) for 21 days will be explored to investigate dynamics of RAR in relation to symptoms over these shorter timeframes.

### Predictor variables

2.5

*Sleep and circadian rhythm disruption predictors*

First and foremost, in all three studies, predictor variables include objectively measured RAR parameters from 14 days of actigraphy (see above). In Study 1 and 2 only, to interpret actigraphy-based sleep variables, participants will also complete the Consensus Sleep Diary
^
85
^ across the 14 days of monitoring. The Van Someren variables Relative Amplitude, Interdaily Stability and Intradaily Variability will be considered for inclusion in all models. Beyond these commonly studied actigraphy variables, Complex System Modelling may identify novel predictive features from RAR (see below).

Given the intimate involvement of environmental light in circadian entrainment,
^
86
^
^,^
^
87
^ predictive models may be improved if the actigraphy signal is augmented with continuous illuminance data [see, e.g.,
88,
94]. Participants in Study 1 and 2 will wear
*MiEye*, a lapel device measuring melanopic and photopic illuminance, for 7 of the 14 actigraphy days.
^
95
^

*Clinical predictors of relapse (Study 1 and 2)*

The present project assumes that objective SCRD data from actigraphy potentially augments, rather than replaces clinical variables in the prediction of BD course.
^
53
^
^,^
^
95
^ Informed by existing literature, five clinical predictors will be included in modelling of RAR-based variables in Study 1 and 2 (clinical predictors will not be included in the models of Study 3 because of concerns about participant burden). Analyses will investigate the impact of, (i) BD subtype, (ii) number of past episodes (measured on the SCID-5-RV), (iii) current use of multiple mood stabilisers by self-report, (iv) residual depressive symptoms measured on the MADRS, and (v) self-reported medication adherence on the Medication Adherence Report Scale.
^
53
^

The decision to elevate these five predictors was informed by a critical review,
^
6
^ by a meta-analysis of risk of subsequent mood episodes by Radua and colleagues,
^
96
^ and the published study most similar in design to the present Study 1.
^
69
^ Each of these predictors has arisen in at least one prospective data set: BD subtype (time to relapse shorter in BD-II
^
96
^), number of past episodes
^
6
^ (iii) current use of multiple mood stabilisers,
^
6
^ (iv) residual depressive symptoms,
^
96
^ (v) medication adherence.
^
6
^ Other variables will be included if a clear rationale can be provided, but a subject-to-variable ratio of 7 to 1 will be preferred.

### Modelling approaches

2.6

As noted above, it is not possible to present a detailed statistical analysis plan until the data to be analysed is clear. Here, we overview data preprocessing plans, present a power analysis for Study 1, and overview the three planned analytic approaches.

*Data preprocessing*

Two categories of missing data will be identified and managed using tailored approaches. For actigraphy data, short and scattered gaps, where the device is worn but a few data points are missing, will be imputed using forward- and backward-fill (FFill/BFill) methods, which are suitable for brief intervals. Longer and continuous gaps, arising from non-wear periods such as device charging or participant non-adherence, will be addressed using a subject-specific model that combines a circadian baseline estimating expected activity at each clock time with a recurrent neural network (RNN) that models short-term deviations from this baseline. A gating mechanism will determine the weighting between these components according to the duration of the gap, giving greater weight to the baseline for longer periods. All imputed data points will be flagged for potential exclusion in sensitivity analyses.

Missingness in clinical data will be handled according to analytic role: participants missing essential outcomes (e.g., relapse status) will be excluded from analyses requiring those outcomes. Clinical predictors and covariates will not be imputed; analyses will use available-case data. Patterns and proportions of missing data will be reported, and sensitivity analyses will assess the robustness of study findings.

*Power Analysis*

Based on the effect size identified by Ferrand et al (see above), a one standard deviation increase in the actigraphy measure increases the risk of relapse by 57% (Hazard Ratio = 1.57). Assuming a sample size of
*N* = 100 participants, initially assuming zero drop-out and then 20% drop-out (
*N* = 80) we used simulation to calculate power estimates based on different Hazard Rate assumptions for a Cox Survival Analysis in Study 1. First, a sample of
*N* = 100 provides 90.6% power to detect a 57% increase in the relative risk of relapse while a sample size of
*N* = 80 provides 75.6% power to detect such an increase. Second, a sample of
*N* = 100 provides 83.0% power to detect a 49% increase in the relative risk of relapse while a sample size of
*N* = 80 provides 83.8% power to detect a 65% increase in the relative risk of relapse. This suggests that even with a 20% dropout the study is nearly sufficiently powered to detect the expected relative risk of relapse (Hazard Ratio = 1.57) and powered to detect a slightly higher relative risk of relapse (Hazard Ratio = 1.65). Note also that the selected sample sizes of
*N* = 100 people with BD in Study 1, 50 in Study 2 (25 BD, 25 matched controls), and 45 in Study 3 (15 manic and 30 depressed) were pragmatic maxima. Recruitment beyond these pragmatic maxima will continue if resourcing permits.

*Cox Survival Analysis*

Cox Survival Analysis will be employed with Elastic Net
^
97
^ to determine variables to include. Relative Amplitude, Intradaily Variability, Interdaily Stability will be included as predictors in a random effects or frailty model of survival time to relapse (across the three epochs of Study 1 and the single epoch of Study 2). Initial time to first episode analysis: Proportional Hazards (Cox) regression with the five clinical covariates listed above. For the modelling of recurrent episodes a Prentice-Williams-Prentice (PWP) model will be used rather than a frailty model because the PWP is appropriate when only a small number of events is likely.
^
98
^

To model the relationship between the actigraphy signal and time to first episode, a two-stage joint survival model will be used. These models analyse time-to-event outcomes that may be linked to biomarkers that are repeatedly measured. A two-stage joint survival model analyses time-to-event outcomes influenced by a longitudinal, time-varying biomarker by fitting two separate models in sequence: a longitudinal model for the biomarker and a survival model for the event. This is a computationally efficient alternative to fully joint models, which can be very time-consuming to fit. The main drawback is that standard two-stage methods can disregard the uncertainty from the first stage’s estimates when they are used in the second, though advanced methods use techniques like multiple imputation to account for this.
^
99
^

Survival analysis has shown that the probability of recovery is significantly lower from major depressive episodes compared to mania or hypomania. Recovery is also less likely from cycling episodes (switching between poles without a recovery period). This means that, ideally, manic and depressive episodes should be analysed together (suggesting a joint survival model for these two types of episode), but it is unclear if we will have sufficient data for this. Decisions will be made on review of the complete dataset and reported in the statistical analysis plan (forthcoming).

*Dynamic Bayesian Network Analysis*

Network analysis is a variant of machine learning designed to illuminate the architecture of complex systems.
^
97
^ In this project, network analysis is used to model potential causal pathways amongst sleep and circadian variables in the prediction of relapse. The analysis generates a graphical representation of nodes (individual characteristics and variables) and edges (connections and links among nodes). Location of nodes and strength/valence of links between nodes represent the specific association between two nodes while controlling for all other variables.

Scott and colleagues recently undertook a pilot study in a sample of young people with emerging BD and produced a network model of RAR variables relative to each other and to phenotypic features of BD.
^
33
^ This study found further support for the importance of robust circadian rhythmicity as measured in Relative Amplitude (see above). However, the authors highlight significant uncertainties in their modelling outcomes, concluding that “… whilst all research findings require replication and confirmation, we stress that this is particularly important in this emerging field of research” (p. 225).

The network analysis of Scott et al. was developed using cross-sectional data, while the present prospective project will permit exploration of how RAR variables change in relation to each other and to other BD symptoms over time. To model these temporal dependencies, Dynamic Bayesian Network Analysis will be applied. Dynamic Bayesian Networks are well suited to representing probabilistic relationships that evolve dynamically and can therefore capture time-dependent causal pathways among RAR, sleep, and clinical variables [see, e.g.,
100,
101]. In addition to Dynamic Bayesian Network Analysis, other machine learning frameworks that complement causal inference with predictive performance will be explored. Specifically, ensemble-based models such as Gradient Boosting Machines and Random Forests, and regularised regression approaches such as LASSO or Elastic Net, will be considered to identify combinations of RAR features that best predict relapse or treatment outcomes.

*Hadaeghi’s Complex System Model of BD*

A key clinical challenge in predicting the course of BD is the condition’s dramatic state changes, most commonly discussed in relation to switching.
^
102
^ It has been proposed that switching and other nonlinear patterns in the course of BD are best understood from a complex system viewpoint, as clinically critical transitions in state space.
^
68
^
^,^
^
103
^ From this perspective, relapse into a new episode and recovery from an acute episode both represent state transitions at which interacting biological and behavioural processes lose or regain stability, and the system shifts to a new state.

Importantly for the theoretical coherence of the present SCRD-grounded project, Hadaeghi’s Complex System Model conceptualises BD as the interaction between two coupled subsystems: the circadian pacemaker and the frontal–limbic system, which governs emotional regulation and behavioural activation. Feedback between these subsystems can maintain stable oscillations (corresponding to episode stability) or, under certain conditions, produce unstable dynamics manifesting as manic or depressive episodes. Endogenous perturbations (e.g., sleep–wake irregularity) or exogenous influences (e.g., psychosocial stress or treatment changes) can shift the system toward instability.

In this project, we implement a complex system-inspired predictive model that adapts the principles of Hadaeghi’s nonlinear dynamical framework to empirical actigraphy data. Rather than directly solving the system of equations, we estimate proxy indicators of system stability from the actigraphy signal. These indicators, which constitute the model’s features, will serve as a bridge between the abstract dynamical system and observed behavioural data.

The extracted indicators will include statistical, time–frequency, and nonlinear features derived from the activity time series and computed over sliding temporal windows, yielding time-varying feature trajectories that reflect changes in system stability. Statistical features (e.g., mean, variance, skewness) will describe overall activity levels; time–frequency features (e.g., spectral power, rhythm amplitude, phase stability) will capture periodicity and circadian patterns; and nonlinear features (e.g., sample entropy, fractal dimension, Lyapunov exponent, correlation dimension, detrended fluctuation analysis) will quantify the complexity and predictability of rest–activity dynamics.

The predictive framework will be implemented using nonlinear dynamic modelling approaches, such as recurrent neural networks (RNNs) or nonlinear autoregressive models, which model sequences of time-indexed feature vectors and are, therefore, well-suited to capturing feedback relationships and temporal dependencies in evolving system dynamics. These models do not explicitly recover the underlying dynamical equations but are designed to learn temporal dependencies in the observed data. These data-driven models are conceptually aligned with Hadaeghi’s formulation of BD as an interacting dynamical system.

The model will be trained to identify patterns and trajectories in these features that precede critical transitions in system stability. In Studies 1 and 2, these transitions will correspond to relapse events among interepisode participants, while in Study 3 they will represent treatment response during acute manic or depressive episodes.

*Input and outcome variables for modelling*

The primary input data for all predictive modelling in Studies 1, 2 and 3 will consist of 14 days actigraphy time-series and derived features extracted through both time-domain and frequency-domain analyses. Feature extraction will include conventional RAR metrics such as the Van Someren variables (Relative Amplitude, Intradaily Variability, and Interdaily Stability), sleep–wake regularity, rhythm phase, and fragmentation, as well as signal-based features obtained from Fourier and wavelet analyses that capture periodicity, spectral power distribution, and nonstationary temporal patterns. Together, these actigraphy-derived metrics will form the principal set of predictors for analyses based on Cox Survival Analysis, Dynamic Bayesian Networks, Hadaeghi’s Complex System Model of BD and other machine learning approaches to be explored.

Auxiliary variables, including demographic and clinical data, will be used to support feature interpretation and to define model outcomes. In Studies 1 and 2, the primary outcome will be relapse, defined as the onset of a new depressive, manic or hypomanic episode meeting DSM-5 diagnostic criteria. Relapse will be identified through structured follow-up interviews using the LIFE (above). Time to first relapse will also be analysed as a survival outcome. In Study 3, the primary outcome will be treatment response, defined as at least a 50% reduction in baseline MADRS or YMRS scores at 8-week endpoint.

These outcome variables will be used to label actigraphy epochs and to train, validate, and compare predictive models of relapse risk and treatment response.

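### Filling long non-wear gaps mainly from the person's own clock-time average raises Interdaily Stability with the share of time filled, so a main predictor partly measures wear time

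*Protocol article*

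**What the plan says.** Section 2.6 (Data preprocessing) separates short scattered gaps, which are forward- or backward-filled, from "Longer and continuous gaps, arising from non-wear periods such as device charging or participant non-adherence". The longer gaps are handled by a "subject-specific model that combines a circadian baseline estimating expected activity at each clock time", together with a recurrent neural network "that models short-term deviations from this baseline". A gate sets the balance between the two "according to the duration of the gap, giving greater weight to the baseline for longer periods".

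On the status of the filled values the article says: "All imputed data points will be flagged for potential exclusion in sensitivity analyses". They are therefore in the main analysis unless later removed.

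The series then feeds everything else. Section 2.5 puts first "objectively measured RAR parameters from 14 days of actigraphy". Section 2.6 (Input and outcome variables) says: "The primary input data for all predictive modelling in Studies 1, 2 and 3 will consist of 14 days actigraphy time-series", along with features derived from them. For the survival analysis, "Relative Amplitude, Intradaily Variability, Interdaily Stability will be included as predictors in a random effects or frailty model".

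**The concern.** Interdaily Stability (IS) is the share of total variance explained by the mean 24-hour profile, that is, how alike the days are. Intradaily Variability (IV) compares hour-to-hour change with total variance. A fill that tends to the person's expected activity at each clock time inserts near-copies of the average day. These have the daily profile but little of the deviation around it. IS is then inflated by construction, and more so the longer the device was off.

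Two things are at stake. First, a named predictor becomes partly a measure of wear time, which adds error to the relapse models. Section 3 (Discussion) expects only about 60 relapses, so there is little room for that. Second, if people who wear the device less also relapse more, the error is differential and makes their rhythms look more stable than they are. Other features computed from the same series, such as entropy, may also be affected; this was not quantified.

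**Working it through.** The article gives no figure on this point to reproduce. It supplies the 14-day record, the fill rule and the predictors. The number of days filled and the signal properties below are assumptions.

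**1. Algebra for IS.** Let B be the variance of the mean daily profile, W the variance of deviations from it, and f the share of the record filled with the profile.

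- Complete record: IS = B/(B + W).
- Filled record: IS' = B/(B + (1 − f)W) = IS/(IS + (1 − f)(1 − IS)), which exceeds IS for any f > 0.
- IS = 0.50, f = 2/14: 0.50/(0.50 + 0.857 × 0.50) = 0.54.
- IS = 0.50, f = 4/14: 0.50/(0.50 + 0.714 × 0.50) = 0.58.

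**2. Algebra for IV.** With dB and dW the mean squared successive differences of profile and deviations, IV = (dB + dW)/(B + W) becomes (dB + (1 − f)dW)/(B + (1 − f)W). This falls when dW/W > dB/B. For a 24-hour cosine sampled hourly, dB/B = 2(1 − cos 15°) = 0.068. With lag-1 autocorrelation r, dW/W = 2(1 − r), so IV falls unless r exceeds about 0.97. This ignores steps at the gap edges, which matter for shorter gaps.

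**3. Simulation, whole-day gaps.** 14 days of hourly data, 400 records per scenario; lag-1 autocorrelation 0.3 to 0.8, lognormal deviation SD 0.5 to 0.8, day-to-day phase SD 0.5 to 1.5 h; baseline weight 1.0 or 0.5, the rest a conditional mean decaying from the gap edges.

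| Days filled of 14 | Change in IS | Change in IV |
|---|---|---|
| 1 (7%) | +0.02 | −0.01 to −0.02 |
| 2 (14%) | +0.04 to +0.05 | −0.01 to −0.05 |
| 4 (29%) | +0.09 to +0.10 | −0.02 to −0.10 |
| 6 (43%) | +0.15 to +0.18 | −0.04 to −0.16 |

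Relative Amplitude moved by at most 0.005. Halving the baseline weight changed little, because a predicted deviation fades within hours of the gap edge.

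**4. Filling against masking, 4 whole days lost** (autocorrelation 0.3, deviation SD 0.8).

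| | Complete | Observed only | Filled |
|---|---|---|---|
| IS | 0.322 | 0.342 | 0.420 |
| IV | 1.116 | 1.126 | 1.028 |

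The formula in step 1 applied to the observed-only value gives 0.342/(0.342 + 0.714 × 0.658) = 0.421, in agreement with the simulated 0.420. The small rise under masking is about what averaging 10 days instead of 14 produces: (1 − 0.322) × (1/10 − 1/14) = 0.019.

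**5. Shorter gaps.** With random 8-hour or evening 6-hour gaps IS still rose, by 0.03 to 0.12; with 8-hour night gaps it rose by less than 0.005. IV was mixed. Evening 6-hour gaps covering 14% of the record moved IV from 0.689 to 0.641 in a scenario with autocorrelation 0.3, but from 0.420 to 0.453 in one with 0.8. One-hour evening gaps every day, filled purely from the baseline, raised IV by 0.008 to 0.035.

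**6. Possible effect on the hazard ratio, non-wear unrelated to risk.** Suppose 20% of participants lose 2 full days, shifting IS by 0.044. The added SD is 0.044 × √(0.2 × 0.8) = 0.018. If the between-person SD of IS is 0.11, the log hazard ratio shrinks by the factor 0.11²/(0.11² + 0.018²), about 2.5%, so that 1.57 becomes about 1.55. If the SD is 0.056, it shrinks by about 9%, to about 1.51. Both SDs and the 20% are assumptions; 1.57 is the article's planning value for an actigraphy measure, borrowed here for IS.

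**The case against.** Five points can be made for the plan.

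- **The text does not call the fill deterministic.** The network's deviations could be random draws, and the gate function is not given. This stands as a limit. But the component whose weight grows is an expected value, and no noise step is described. With point predictions, even half weight on the baseline left the whole-day result almost unchanged.
- **The article does not say outright that IS and IV come from the filled series.** True, but filled points that are only flagged for possible removal in sensitivity analyses are otherwise in the main data.
- **A reader might infer that the fill always lowers IV, so that two of the three named predictors are always biased towards a healthier rhythm.** The documents do not support that. Device charging is named as a cause of long gaps and may last only hours; at that length the direction for IV depends on time of day and autocorrelation.
- **A reader might also infer that people approaching relapse are given artificially stable rhythms.** Nothing in the article links non-wear to mood or relapse. In Studies 1 and 2, baseline actigraphy is worn by people screened as not in an episode; later Study 1 epochs can include symptomatic people. The link is possible but unshown. Without it, step 6 gives only modest attenuation.
- **Plain masking is not always better.** With 10-hour daytime gaps on 6 of 14 days, filling shifted IS by +0.14 and masking by +0.18 to +0.19. This stands and changes the remedy. In other simulated records with daytime non-wear, masking gave +0.13 to +0.15 and filling +0.12 to +0.13, while weighting clock hours equally cut the shift to about +0.02 to +0.03.

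Minimum-wear rules and similar detail may properly sit in the study-level protocols or the forthcoming analysis plan. Their absence here is not part of this point.

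**Conclusion.** The point holds for IS. As described, the fill raises it in proportion to the share of time filled: about +0.04 for 2 whole days of 14 and about +0.10 for 4, against about +0.01 and +0.02 when those days are masked. For IV the effect is smaller and holds for whole-day gaps only. Relative Amplitude is essentially unaffected.

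The certain consequence is measurement error that depends on wear time. Differential bias follows only if non-wear is related to relapse risk. The figures assume that the baseline dominates in long gaps and that no residual noise is added. The article gives no non-wear share, gate function or distribution of IS. Expressing the shift in SD units therefore rests on an assumed SD: for 2 days it is about 0.6 to 1 SD against the spread of the simulated records, but 0.4 SD if the real spread is 0.11.

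The planned optional exclusion of flagged points could reveal the problem, but it leaves the bias in the main result and in the trained models.

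**What to change.** Reverse the order of the two analyses, using the imputation flags already planned.

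- **Main analysis:** compute IS and IV from observed wear time only. Weight clock hours equally, or drop days with substantial non-wear, because plain masking also biases IS when non-wear clusters at certain hours.
- **Sensitivity analysis:** the version computed from the filled series.
- **Sequence models and nonlinear features that need a gap-free series:** impute several times with random residual noise, so that filled stretches carry realistic deviation.

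The cost is a little more preprocessing work and a change of text in the forthcoming analysis plan. Some precision is lost, and some epochs with little wear may drop out; how many cannot be told from the article.
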